### Date collection methods and management

CANTAB is a computer-administered battery of tasks, and the primary outcome variables from the CANTAB tasks will be automatically calculated by the software. A clinical senior psychiatrist blinded to the group allocation will assess the severity of depressive symptoms using HAMD-24.

All participant demographic and scale related results will be recorded in the case report form (CRF). For patient privacy, irrelevant personal information like names, contact numbers, and addresses will be omitted during data entry, using patient numbers for identification. The original CRFs are securely stored and accessible only to the project leader and principal investigator.

Our trial does not have a data monitoring committee, but the subject group has a dedicated person to oversee. We will notify patients to come for tDCS via WeChat (a popular social communication app in China) and reimburse their transportation costs to improve patient compliance.

## Statistical analysis

### Sample size

Based on primary cognitive function outcome—the SRM correct rate [5], we calculated the sample size. Sample size was determined via PASS software (PASS 15, NCSS, LLC. Kaysville, UT, USA) for a power of 0.80 and a two-tailed α level of 0.05. Parameters were derived from a prior study [5] (mean SRM correct rate at 1-month follow-up: 64.67%, SE: 3.88, SD: 15.03, dropout rate: 37.5%). Calculations yielded permissible error (δ) = 16.20 (20% of mean), and σ = 15.03. Recruitment won't exceed original participants; thus, 24 patients per group are needed. Thus, 24 patients per group are needed. Based on a 20% dropout rate, each group ended up with 30 participants.

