### Study design and setting

This is a randomized, double-blind, sham-controlled, interventional trial. 60 eligible participants will be recruited within two days after the last ECT session and randomly allocated into two groups in a 1:1 ratio: active tDCS (intervention group) and sham tDCS (control group). Assessments will be conducted at the following time points: before the first tDCS session (T0), immediately after the last tDCS session (T1), 2 weeks post-tDCS (T2), and 4 weeks post-tDCS (T3), using the Cambridge Neuropsychological Test Automated Battery (CANTAB). Table 2 shows schedule of enrolment, intervention, and assessments. Throughout the study, there was no interference or restriction for the patient ‘s physician in charge to adjust psychiatric medications according to the patient’ s condition. Figure 1 represents the research procedure schematically.

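### The planning difference of 16.20 is not 20% of the stated mean of 64.67%, and with the stated σ, α and power it needs 15 evaluable patients per group, so the origin of 24 cannot be traced

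*Protocol article*

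**What the plan says.** All of this stands in the Sample size section of the protocol article. The calculation rests on the primary outcome, the Spatial Recognition Memory (SRM) correct rate, and was run in PASS "for a power of 0.80 and a two-tailed α level of 0.05". The inputs come from one earlier study: "mean SRM correct rate at 1-month follow-up: 64.67%, SE: 3.88, SD: 15.03, dropout rate: 37.5" (per cent). The article then sets the difference and the standard deviation: "Calculations yielded permissible error (δ) = 16.20 (20% of mean), and σ = 15.03". The group size follows with this reason: "Recruitment won't exceed original participants; thus, 24 patients per group are needed". A dropout allowance is added last: "Based on a 20% dropout rate, each group ended up with 30 participants". Study design and setting confirms 60 participants, "randomly allocated into two groups in a 1:1 ratio".

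**The concern.** Two links in the chain do not hold as printed. The difference does not match its own label, because 20% of the one mean supplied is not 16.20. The group size also does not follow from the printed difference, σ, α and power. The reason offered for 24, a ceiling tied to the earlier study's participants, is not a power argument. In addition, two dropout rates appear, 37.5% and 20%, and only the second is said to have been applied.

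This is the article's only power statement, and it concerns the primary outcome. As written, the difference the trial was sized to detect could be 12.93 or 16.20 points, and the number of evaluable patients required could be 23 or 15. That matters most for judging how much loss to follow-up the design can absorb, a risk that the article's own limitations raise because discharged patients must travel to the hospital for stimulation.

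**Working it through.** **Inputs (Sample size section).** Mean 64.67, SE 3.88, SD 15.03, prior-study dropout 37.5%, δ = 16.20, σ = 15.03, two-sided α = 0.05, power 0.80, 20% dropout allowance. Allocation is 1:1. The article does not name the test behind the PASS run; I assume a two-sample comparison of means.

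**1. The figures that reproduce.** 24/(1 − 0.20) = 30 per group, and 2 × 30 = 60. The last step is correct.

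**2. The difference.**
- 0.20 × 64.67 = 12.93
- 16.20/64.67 = 0.2505, about 25%
- 16.20/0.20 = 81.0, a mean not given in the article
- Gap: 16.20 − 12.93 = 3.27 points, too large for rounding

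**3. Number per group from δ and σ.** By normal approximation, n = 2(1.960 + 0.842)²σ²/δ².
- δ = 16.20: 2 × 7.849 × 225.90/262.44 = 13.5, so 14. The exact noncentral-t calculation gives 14.5, so 15.
- δ = 12.93: 2 × 7.849 × 225.90/167.29 = 21.2, so 22. The exact noncentral-t calculation gives 22.2, so 23.

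Neither gives 24. Under δ = 12.93 the t-test figure is one short of it.

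**4. Power with 24 evaluable per group.** The noncentrality is (δ/σ)√(24/2), on 46 degrees of freedom.
- δ = 16.20: 1.078 × 3.464 = 3.73, power 95.5%
- δ = 12.93: 0.861 × 3.464 = 2.98, power 83.1%

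**5. Where 24 could come from, at the stated α and power.**
- *Inflation for 37.5% dropout:* 15/(1 − 0.375) = 24 exactly. Adding 20% to reach 30 would then allow for dropout twice, at two rates. Inflating 15 once for 20% gives 15/0.8 = 18.75, so 19.
- *Size of the earlier study:* (15.03/3.88)² = 15.0 patients followed up, and 15/0.625 = 24 enrolled. This fits the remark about the original participants but is not a power calculation.
- *δ = 12.93:* 23 by t-test, close to 24. The printed 16.20 would then be the error.

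At δ = 16.20, 24 is also what a t-test needs for 95% power, but the article states 0.80.

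**6. Sensitivity to retention.** If the earlier study's 37.5% loss recurred, 30 × 0.625 = 18.75, so 18 to 19 per group would remain. Power is then about 88–90% at δ = 16.20 and about 71–73% at δ = 12.93.

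**The case against.** The strongest reply is that 24 is not out of reach of the listed parameters. The same parenthesis that gives the mean and SD also gives the 37.5% dropout, and 15/(1 − 0.375) is exactly 24; with δ = 12.93 the required 23 is almost 24. Either way the planned number is adequate and nothing about the conduct of the trial changes. This stands as far as it goes. It rules out saying that the inputs cannot yield 24. It does not repair the paragraph, because each route needs a step the article does not state or a correction to a figure it prints.

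Four stronger readings are tempting, and the documents do not support them:

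- *The trial is underpowered.* It is not shown to be. At the planned retention both candidate differences exceed 80% power.
- *Dropout was counted twice.* This follows only if the 37.5% route was used, and the article never says so. If 24 came from the earlier study's size or from δ = 12.93, the 20% is the only allowance made.
- *The difference is overstated by 3.27 points.* That presumes 64.67 and 20% are right. The percentage or the base mean could equally be the misprint; 16.20 is exactly 20% of 81.0. The article alone cannot settle it.
- *A reader could not tell which difference a non-significant result excludes.* What a result excludes is read from its confidence interval, not from the planning difference.

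**Conclusion.** The paragraph is wrong as written. The stated difference and its label disagree by 3.27 points (16.20 against 12.93), and the printed δ, σ, α and power lead to 15 evaluable patients per group rather than 24. If 16.20 is meant, power at 24 evaluable is about 95%, not the stated 80%. If 20% of 64.67 is meant, 23 are needed and 24 gives 83%. The article does not show which element is in error or how 24 was obtained.

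The defect is an incorrect design figure and a derivation that cannot be followed. The power figures assume a two-sample t-test, σ = 15.03 taken as given, and 24 evaluable patients per group. They fall below 80% only in the combination of δ = 12.93 and 37.5% loss, which is not what the article plans for.

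**What to change.** Rewrite the Sample size paragraph and keep the 60 patients. The choice of difference belongs to the authors and should reflect what they actually used.

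1. State the intended δ and the mean it is based on, with the matching number and power:
   - If δ = 12.93 (20% of 64.67): 23 evaluable per group for 80% power; 24 gives 83%.
   - If δ = 16.20: describe it as about 25% of 64.67 (exactly 25% would be 16.17), or give the correct base mean; 15 evaluable per group for 80% power; 24 gives 95%.
2. Show how 24 is obtained, and replace the statement about not exceeding the original participants as its basis.
3. Allow for dropout once, at one stated rate, and say what part, if any, the 37.5% played.

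The cost is the wording of one paragraph. No patients are added: even the larger requirement, 23/0.8 = 28.75, so 29 per group, lies within the planned 30.

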### Statistical methods

To assess the normality or approximate normality of the data, we will employ a combination of histograms and the Shapiro–Wilk test. For normally or approximately normally distributed data, we will report the results as mean ± standard deviation (SD). If the data exhibit skewness, we will express the results as medians and quartiles. Categorical data will be presented as absolute numbers and percentages. Appropriate statistical tests, such as t-tests, nonparametric tests, or chi-square tests, were used in assessing differences in baseline characteristics between groups.

Consideration of repeated measurement data, we employed three strategies for presentation. Firstly, a line graph was utilized to depict values (whether rates or averages) at distinct time points. Secondly, we applied mixed regression models to assess both between-group and time effects for both primary and secondary outcomes. We will employ the stepwise selection approach to construct parsimonious regression models. These adjustments will account for additional factors that may potentially influence these associations, including age, ECT sessions, HAMD-24 score, SDS score, gender, current medication usage, disease duration, etc. Age and gender were entered in all models regardless of their statistical significance. Thirdly, we examined simple effects at different time points and adjusted *p*-values to reduce the risk of false positives.

No interim analysis and subgroup analysis will be performed. Transforming the data into a longitudinal format to meet the fitting requirements of mixed regression models. The statistical analysis of our data will be conducted using SPSS version 25.0 and R version 4.1.3. We define statistical significance as a two-tailed *p*-value of less than 0.05.

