## Method

### Objective

The primary objective of this study is to determine whether the implementation of active tDCS after completing the ECT course accelerates recovery from the CSEs, especially the spatial recognition memory.

Secondary, the study aims at examining the long-term (after 4 weeks) effects in improving cognitive function and the whether the implementation of tDCS after the ECT course decrease the relapse of depressive symptoms.

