## Discussion

This is the first RCT aimed at using tDCS to assist in the recovery of CSEs caused by ECT in depression patients. Given that CSEs might hinder patients from opting for ECT [60], identifying a rehabilitation strategy could assist patients in alleviating these concerns.

Depressive patients exhibit an imbalance in cortical metabolism between the two hemispheres, with lower metabolism observed in the left frontal lobe compared to the right frontal lobe [61, 62]. ECT can induce a short-term reduction of CBF and metabolism in frontal lobe, but this alteration subsequently normalizes within around one month [13].

By utilizing the anode at left DLPFC and the cathode at right DLPFC, tDCS aims to rectify the cortical imbalance in depression, ultimately ameliorating depressive symptoms [61]. Although the mechanisms underlying the impact of tDCS on cognitive function remain not entirely clear, early research suggests that tDCS may elicit long-term effects extending beyond the stimulation period [49, 63, 64]. Otherwise, these enduring effects are likely mediated through the modulation of N-methyl-D-aspartate and gamma-aminobutyric acid receptor activity [65, 66].

Cognitively, depression in the elderly is intricately linked with dementia; past studies have suggested that depressive symptoms might be a precursor to dementia [67, 68]. Despite improvements in depressive symptoms, elderly patients often continue to exhibit deficits in visuospatial ability, information-processing speed, and delayed memory [69]. This complexity adds to the challenge of distinguishing whether cognitive deficits in elderly patients post-ECT are due to ECT itself or pre-existing conditions. Further research indicates that while ECT treatment may lead to short-term cognitive decline in elderly patients [70], there is potential for long-term cognitive improvement [71]. Therefore, enhancing cognitive function during symptom remission in elderly patients with depression is of critical clinical importance, a goal that requires further dedicated efforts [72].

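### No primary visit or contrast is fixed for spatial recognition memory: objective, outcome, sample size and planned analysis point to different tests

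*Protocol article*

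**What the plan says.** All references are to the Protocol article.

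- **Objective.** The primary aim is to learn whether "implementation of active tDCS after completing the ECT course accelerates recovery from the CSEs", with spatial recognition memory singled out. Effects after 4 weeks are listed as a secondary aim.
- **Primary outcome.** A change in SRM, scored as percentage correct. No visit is given. SRM is measured before stimulation (T0), at the end of stimulation (T1), and 2 and 4 weeks later (T2, T3).
- **Sample size.** It is planned "for a power of 0.80" and a "two-tailed α level of 0.05". The inputs come from an earlier study ("mean SRM correct rate at 1-month follow-up: 64.67" per cent) and give "permissible error (δ) = 16.20 (20% of mean), and σ = 15.03". The result is 24 per group, raised to 30 for dropout.
- **Statistical methods.** Three ways of presenting the repeated measures are listed: a line graph; a model step ("we applied mixed regression models to assess both between-group and time effects for both primary and secondary outcomes"); and a last step in which "we examined simple effects at different time points and adjusted" the p-values. None is called the primary analysis. The adjustment method and the set of time points are not named.

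**The concern.** Whether recovery is accelerated depends on how the difference between arms develops after T0. A test of it needs either a group-by-time term or a group difference at a stated post-baseline visit. The text states neither.

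Four sections address the primary question, and each implies something different: a speed of recovery, a change with no endpoint visit, a level at one month, and a group effect alongside a time effect. The time effect on its own says nothing about tDCS, because both arms are expected to recover.

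Two things are at stake. First, an analyst could choose among a main effect, an interaction and several visit-specific differences after seeing the data. Second, the stated power belongs to a single unadjusted comparison at one time, which is not identified as the primary analysis.

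**Working it through.** **1. The plan's own figure.** Inputs from Sample size: δ = 16.20, σ = 15.03, two-sided α = 0.05, power 0.80.

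- Normal formula: n = 2 × (1.960 + 0.842)² × (15.03/16.20)² = 13.5, so 14 per group; the exact t calculation gives 15.
- Applying the quoted 37.5% dropout: 15/(1 − 0.375) = 24. Then 24/(1 − 0.20) = 30. The stated 24 and 30 are reproduced this way, though the text does not explain the first step.
- 20% of 64.67 is 12.93, while 16.20 is 25% of it. With δ = 12.93 the formula gives 22 (exact t: 23). Because the text supports both values, both are carried below.
- Power of one unadjusted comparison at one visit, 24 per group: 0.955 at 16.20 and 0.83 at 12.93.

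The powered quantity is therefore a difference in SRM levels at one time.

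**2. Which visit was powered?** The inputs are labelled 1-month follow-up. If that is counted from the last ECT (an assumption; the source is not at hand), it falls near T2, because T1 comes about two weeks after ECT and T2 about four. If it is matched to the 4-week visit, it is T3, which serves a secondary aim. The text ties it to no visit.

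**3. Power of the candidate tests.** Assumptions: 24 per group, SD 15.03 at every visit, and equal correlation ρ = 0.4–0.5 between visits (the document gives none).

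*Group main effect averaged over T0–T3.* The SD of a patient's four-visit mean is 15.03 × √((1 + 3ρ)/4), which is 11.15 at ρ = 0.4 and 11.88 at ρ = 0.5. The true difference at T0 is zero because T0 precedes stimulation.

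- Fading pattern (full at T1, half at T2, none at T3): average = δ × (0 + 1 + 0.5 + 0)/4, which is 6.08 or 4.85.
- Sustained pattern (full at T1–T3): average = δ × 3/4, which is 12.15 or 9.70.

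*One visit, adjusted for T0.* Residual SD = 15.03 × √(1 − ρ²), which is 13.78 at ρ = 0.4 and 13.02 at ρ = 0.5.

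*T1 at 0.05/3, not adjusted for T0.* SD 15.03.

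| Test | δ = 16.20 | δ = 12.93 |
|---|---|---|
| Main effect with T0, fading | 0.41–0.46 | 0.28–0.31 |
| Main effect with T0, sustained | 0.93–0.96 | 0.79–0.84 |
| One visit, adjusted for T0, α 0.05 | 0.98–0.99 | 0.89–0.92 |
| T1, unadjusted for T0, α 0.05/3 | 0.89 | 0.69 |

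For the main effect the lower figure belongs to ρ = 0.5; for the baseline-adjusted contrast it belongs to ρ = 0.4.

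Over the wider range ρ = 0.3–0.7, the main effect under fading has power 0.51–0.34 (16.20) and 0.36–0.24 (12.93). The baseline-adjusted contrast has 0.97–1.00 and 0.86–0.98.

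**4. Type I error if more than one route counted.** Suppose success meant either the main effect at 0.05 or any Bonferroni-adjusted simple effect at T1–T3. Simulation under no effect gives an error rate of about 7–7.5% for ρ = 0.4–0.5. The protocol does not state this rule; the figure shows what leaving the choice open could cost.

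**The case against.** The strongest reply is that the text does not commit to a poor test.

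- **Pooling over T0–T3 is an inference.** A reader might take the group effect as averaged over all four visits. The document does not say so, nor that T0 is among the model's outcomes. Calling the outcome a change suggests that T0 is a baseline, and simple effects usually presuppose an interaction, so one may be intended. This stands: dilution is conditional on a reading the text permits but does not state.
- **A fading effect is only one scenario.** The Discussion remark that "this alteration subsequently normalizes within around one month" might suggest that sham patients catch up by T2 or T3. That remark concerns frontal blood flow and metabolism. The Introduction says spatial recognition memory impairment may last beyond a month, and the Discussion allows for tDCS effects that outlast stimulation. The protocol therefore does not predict catch-up on SRM.
- **Adjusted simple effects need not fall short of 80% power.** At the stated 16.20 a T1 test at 0.05/3 has 0.89. It falls to 0.69 only at 12.93 without baseline adjustment; with adjustment it has about 0.78–0.83.
- **P-values are to be adjusted**, and the method of adjustment can be left to an analysis plan.

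None of this supplies the missing element. The primary visit and contrast belong in the protocol, and the four sections that bear on them do not agree.

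**Conclusion.** The point holds in limited form: no deciding test, visit or contrast is fixed for the primary outcome; the group-by-time term is unstated; and the single-time comparison that was powered is not identified as the primary analysis. This rests on the text alone and needs no assumption.

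The size of the consequence does need assumptions: equal correlation of 0.4–0.5, SD 15.03 at every visit, 24 completers per arm, and a chosen effect pattern. Across the two differences, power runs from 0.28–0.46 (main effect including T0, fading effect) to 0.89–0.99 (one baseline-adjusted visit). For a sustained effect the main effect loses much less. The documents do not support saying that the planned analysis is certainly underpowered or that its error rate certainly exceeds 5%.

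**What to change.** In Primary outcome and Statistical methods, name one primary contrast at two-sided 0.05: the active-minus-sham difference in SRM percentage correct at one pre-named post-baseline visit. T1 is the natural choice, since the aim is acceleration and the 4-week effect is already secondary. Another visit could be defended if it is fixed in advance.

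Estimate the contrast from a mixed model with SRM at T1–T3 as outcomes, T0 SRM as covariate, and group, visit and group-by-visit terms. Make the other visits secondary. State that neither the time effect nor a group effect that includes T0 will be used as evidence of efficacy. In Sample size, say which visit the calculation refers to.

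The cost is wording only: the same assessments, no added patients, and power at or above the stated 0.80 with 24 per arm under the assumptions above. The downside is that an effect emerging only at another visit would count as secondary.

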### Outcome

To assess cognitive changes, we will employ the CANTAB, a tool previously demonstrated to be highly sensitive in evaluating the cognitive side effects of ECT [5, 6]. Additionally, we have chosen a set of five tests designed to assess frontal lobe function. To mitigate potential learning effects, different parallel versions of the same test will be employed during various assessment phases. Assessments of cognitive function and depressive symptoms will be conducted before the first tDCS session (T0), immediately after the last tDCS session (T1), 2 weeks post-tDCS (T2), and 4 weeks post-tDCS (T3). The detailed visit procedure is shown in Table 2.

**Table 2 Tab2:** Schedule of enrolment, intervention, and assessments

	Enrolment	Baseline	Intervention	Follow-up	
		Before tDCS	After tDCS	after 2 weeks	After 4 weeks
Time point		T0	T1	T2	T3
Enrolment					
Eligibility screening	√				
Informed consent	√				
Allocation	√				
Demographic data		√			
Intervention					
Active tDCS			√		
Sham tDCS			√		
Assessments					
CANTAB					
SRM		√	√	√	√
SWM		√	√	√	√
RVP		√	√	√	√
VRM		√	√	√	√
SOC		√	√	√	√
HAMD-24		√	√	√	√
SDS		√	√	√	√
tDCS-AEQ^a^			√		
Blinding			√		

*a: test after every tDCS session*

*CANTAB: Cambridge Neuropsychological Test Automated Battery, HAMD-24: Hamilton depression rating scale; RVP: Rapid visual information processing; SDS: Self-rating depression scale; SOC: Stockings of Cambridge; SRM: Spatial recognition memory; SWM: Spatial working memory; VRM: Verbal Recognition Memory; tDCS, transcranial direct current stimulation; tDCS-AEQ: Transcranial direct current stimulation adverse effects questionnaire*

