### Second outcome

Spatial Working Memory (SWM) assesses the subject's ability to retain and manipulate spatial information in working memory. The outcome measures include between errors, within errors, and strategy employed. A high strategy score represents poor use of strategy, and a low score equates to effective use.Verbal Recognition Memory (VRM) evaluates immediate and delayed verbal information memory. Outcome measures include the total number of correct words in the free recall phase, the total of all correctly identified words in the immediate recognition phase, and the delayed recognition phase.Rapid Visual Information Processing (RVP) assesses visual sustained attention. Outcome measures include mean latency and total correct responses.Stockings of Cambridge (SOC) evaluates spatial planning and spatial working memory. Outcome measures include the number of n-move problems solved in the minimum moves, mean moves for n-move problems, mean initial thinking time for n-move problems, and mean subsequent thinking time for n-move problems.Assessing the degree of depressive symptom with the Hamilton Depression Rating Scale (HAMD-24) [56] and the Self-rated Depression Scale (SDS) [57, 58].

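### Covariates for the treatment comparisons are chosen stepwise from an open list that protects only age and gender and does not restrict depression scores or medication to T0 values

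*Protocol article*

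**What the plan says.** All of the following is in the protocol article.

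- **Scope (Statistical methods).** "we applied mixed regression models to assess both between-group and time effects for both primary and secondary outcomes".
- **Selection (Statistical methods).** "We will employ the stepwise selection approach to construct parsimonious regression models". No entry or removal rule is given.
- **Candidates (Statistical methods).** Factors that may influence the associations, "including age, ECT sessions, HAMD-24 score, SDS score, gender, current medication usage, disease duration, etc". The list is left open at its end, and no time point is attached to the two depression scores or to medication.
- **Protected terms (Statistical methods).** "Age and gender were entered in all models regardless of their statistical significance". Nothing is said about keeping group, visit or their interaction.
- **Status of the depression scores.** HAMD-24 and SDS are listed under Second outcome. The Outcome section and Table 2 have them measured at T0, before the first stimulation, and again at T1, T2 and T3. The Objective section makes reduced relapse of depressive symptoms a secondary aim.
- **Medication (Study design and setting).** Throughout the study "there was no interference or restriction for the patient" and the treating physician in adjusting psychiatric drugs.

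**The concern.** Choosing covariates by their association with the outcome is a way to build a prediction model. In a randomised comparison it makes the adjusted treatment effect depend on which variables happen to cross a threshold. With 60 patients and an open list, two analysts could follow the same text and report different estimates, and the reported p-value takes no account of the search.

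The second problem is timing. The data are to be reshaped to long form, with one row per visit, and nothing stops the same-visit HAMD-24, SDS or medication from being used as a covariate. Such a value can be a consequence of treatment. Adjusting for it takes out the part of the group difference that runs with mood. It can also create a difference where none exists, if unmeasured patient factors drive both mood and memory. The same list serves the secondary outcomes, so SDS could be used to adjust the HAMD-24 comparison and the reverse, which bears directly on the relapse aim.

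**Working it through.** No figure in the plan is at issue, so there is none to reproduce. The check asks when the stated method does harm, and how much.

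**Inputs from the Sample size section:** SD 15.03, stated difference 16.20, 30 per group. **Assumptions, not in the documents:** the SRM–HAMD-24 correlation at a visit, the size of any tDCS effect on mood, and the selection rule.

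**1. Adjusting for same-visit HAMD-24 (one visit, linear model)**

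Adjusted effect = unadjusted effect − (slope of SRM on HAMD-24) × (group difference in HAMD-24).
Per SD of HAMD-24 the slope has size r × 15.03. With a mood effect of 0.5 SD, the amount removed is r × 15.03 × 0.5.

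- r = 0.3: 0.3 × 15.03 × 0.5 = 2.25 points; 2.25 / 16.20 = 14%.
- r = 0.5: 0.5 × 15.03 × 0.5 = 3.76 points; 3.76 / 16.20 = 23%.

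This takes HAMD-24 as selected into the model.

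**2. Simulation of the repeated-measures model**

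Settings: 30 per group, three post-baseline visits, random-intercept generalised least squares, backward selection at p < 0.05, age and gender always in, 4,000 runs per setting. The Monte Carlo SE of an error rate is about 0.004.

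| Setting | Result |
|---|---|
| No true effect, age and gender only | type I error 0.058 |
| No true effect, T0 candidates, group kept | type I error 0.056 |
| True effect 16.20, age and gender only | mean estimate 16.33 |
| True effect 16.20, T0 candidates, group kept | mean estimate 16.34 |
| No true effect, same-visit scores, mood effect 0.5 SD | bias −0.6 points, type I error 0.062 |
| No true effect, same-visit scores, mood effect 0.8 SD | bias −1.1 points, type I error 0.085 |
| Direct effect 8, mood also acts on SRM (0.3 SD per SD), mood effect 0.5 SD | total 8 + 0.3 × 0.5 × 15.03 = 10.3; estimated 7.1 |
| Same, mood effect 0.8 SD | total 8 + 0.3 × 0.8 × 15.03 = 11.6; estimated 6.5 |
| Group open to selection, T0 candidates, true effect 8 | mean when retained 9.3 (8.1 if group is kept) |
| Group open to selection, T0 candidates, true effect 4 | mean when retained 7.7 |

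In the two settings where mood acts on memory, the estimate falls below even the direct effect of 8. The shared patient factor adds bias on top of the mediated part. Where group was open to selection and there was no true effect, the rejection rate was 0.053, so the harm there is exaggeration of retained estimates rather than excess false positives.

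**3. Simpler simulation of selection alone**

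Ordinary regression, 48 patients, no true effect, age and gender always in, 5 to 12 irrelevant candidates, 4,000 runs (Monte Carlo SE about 0.35 percentage points). Type I error was 5.5 to 6.6% with entry at p < 0.05, and 6.9 to 8.7% with a looser AIC-like rule.

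**The case against.** The strongest defence is that the text can be read harmlessly. The other named candidates (age, gender, number of ECT sessions, disease duration) are all fixed before stimulation, so T0 values of HAMD-24, SDS and medication would be the natural companions. Long form does not imply time-varying covariates, since baseline values are routinely repeated across rows. Models said to assess between-group effects presumably contain group. On that reading the simulation shows no material bias and no material inflation. This stands, and it limits the point. It does not remove it, because the text fixes neither the timing nor the group term, and stepwise selection is itself stated.

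Several stronger readings are tempting but not supported:

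- **That the covariates are post-randomisation values.** The plan does not say so, and T0 values exist. Table 2 does place allocation before T0, but a T0 value still precedes any stimulation.
- **That the p-value is invalid.** With T0 candidates and group kept in, type I error was 0.056 against 0.058 without selection. The 6.9 to 8.7% needs an entry rule that the plan does not state, in a simpler model than the one planned.
- **That the protocol expects this trial's montage to lift mood.** The Discussion says "tDCS aims to rectify the cortical imbalance in depression, ultimately ameliorating depressive symptoms", but of a cathode over the right DLPFC. This trial's cathode is over the right supraorbital region (Intervention section). The relapse aim is the better evidence that an effect on mood is contemplated.
- **That baseline SRM is left out.** The primary outcome is change in SRM and the models include time, so T0 may already be one of the responses.
- **That 17 to 29% of the effect is lost.** That takes 12.93 (20% of 64.67) as the denominator. The plan's stated difference is 16.20.

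**Conclusion.** The point holds in a conditional form. The plan commits the primary and secondary treatment comparisons to outcome-driven selection from an open list, guarantees only age and gender, and leaves the timing of HAMD-24, SDS and medication unfixed. The nominal p-value ignores that selection.

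The size depends on how the text is carried out. With T0 covariates only and group kept in, the inflation is small. If same-visit depression scores enter, about 2.3 to 3.8 points (14 to 23% of 16.20) are removed under the assumed correlation of 0.3 to 0.5 and mood effect of 0.5 SD. If group is itself a candidate, estimates that survive selection are too large. The correlations, mood effects and selection rules are assumptions. The documents establish that the plan allows these paths, not that they will be taken.

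**What to change.** Drop stepwise selection for every treatment comparison. State one mixed model in advance:

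- Group, visit and group-by-visit are always in the model.
- Age, gender and a short, closed, named list of covariates recorded at or before T0 are included whatever their significance. Number of ECT sessions and T0 HAMD-24 are examples; the exact choice is the investigators'.
- The T0 value of the outcome is used once: either as a covariate with T1 to T3 as responses, or as a response with the T0 group means constrained equal. It should not be both.
- The same structure is used for the secondary outcomes, each with its own T0 value.
- Any model containing HAMD-24, SDS or medication recorded after T0 is labelled exploratory.

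The change should be made before unblinding. HAMD-24, SDS and the cognitive tests are already scheduled at T0, so it costs wording and a few degrees of freedom for the fixed covariates.
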